## Introduction

1

Pneumonia is one of the leading causes of intensive care unit (ICU) admissions. Among pneumonia patients, acute respiratory distress syndrome (ARDS) is the most common etiological factor leading to respiratory failure. Since March 2020, worldwide ICU admissions were mainly ARDS patients infected with coronavirus disease (COVID-19).

Within intensive care units, approximately 10% to 15% of admitted patients, and up to 20% of mechanically ventilated patients meet ARDS criteria.^[1–3]^

In Qatar, between February 28 and April 18, 2020, 5685 cases of COVID-19 were identified. More than 90% were with minimal symptoms or asymptomatic, with 2.0% required critical care support.^[4]^ COVID-19 patients with existing comorbidities (mainly hypertensive and diabetes) had higher C-reactive protein (CRP) levels (inflammatory response), a higher ICU admission rate, extended hospitalization, and more oxygen use.^[5,6]^ On the other hand, patients with eosinophilia had a lower level of CRP, milder clinical course and better disease outcomes compared to those without eosinophilia.^[7]^

The Berlin definition of ARDS requires that all the following criteria be present for diagnosis.^[8,9]^

1.Respiratory symptoms must have begun within 1 week of a known clinical insult, or the patient must have new or worsening symptoms during the past week.2.Bilateral opacities must be present on a chest radiograph or computed tomographic (CT) scan. These opacities must not be fully explained by pleural effusions, lobar collapse, lung collapse, or pulmonary nodules.3.The patient's respiratory failure must not be fully explained by cardiac failure or fluid overload. An objective assessment (echocardiography) to exclude hydrostatic pulmonary edema is required if no risk factors for ARDS are present.4.A moderate to severe impairment of oxygenation must be present, as defined by the ratio of arterial oxygen tension to the fraction of inspired oxygen (PaO_2_/FiO_2_). The severity of the hypoxemia defines the severity of the ARDS:Mild ARDS – The PaO_2_/FiO_2_ is >200 mm Hg, but ≤300 mm Hg, on ventilator settings that include positive end-expiratory pressure (PEEP) or continuous positive airway pressure (CPAP) ≥5 cm H_2_O.Moderate ARDS – The PaO_2_/FiO_2_ is >100 mm Hg, but ≤200 mm Hg, on ventilator settings that include PEEP ≥5 cm H_2_O.Severe ARDS – The PaO_2_/FiO_2_ is ≤100 mm Hg on ventilator settings that include PEEP ≥5 cm H_2_O

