### Eligibility criteria

4.2

1.Patients with ARDS as per Berlin definition2.Age: 18 years and above

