### Exclusion criteria

4.3

1.Patients with altered sensorium [Glasgow Coma Scale less than 13]2.Pregnant patients3.Hemodynamic instability4.Morbidly obese5.Patients with tracheostomy6.Severe acidosis [PH less than 7.15]7.Patients with glaucoma8.Patients with a history of vertigo

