### Outcomes measures

4.4

Primary outcome measure:

1.Need for endotracheal intubation [ time frame: 6 weeks].Number of patients requiring endotracheal intubation after application of helmet device

Secondary outcome measures:

1.Improvement in oxygen saturation [time frame: 2 weeks]Improvement of oxygenation defined as “PaO2/FiO2 ≥ 200 or increase from baseline by 100”.2.Ventilator-free days [time frame: 28 days]Duration of mechanical ventilation via endotracheal tube.3.Intensive care unit length of stay [time frame: 4 weeks]The number of days admitted to the intensive care unit.4.Overall mortality [time frame: 90 days]Death from any cause during hospitalization at the time of enrollment.5.Need for proning [time frame: up to 24 weeks]Need for proning during the hospital stay.6.ICU mortality [time frame: 28 days]Death from any cause during ICU hospitalization at the time of enrollment.7.Patient tolerability [time frame: 28 days from randomization]The degree to which overt adverse effects of a drug can be tolerated by a patient, including feeding tolerance.

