### Sample Size & Recruitment

4.6

Sixty patients will be recruited after randomizing the selected patients with odd or even numbers.

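### The oxygenation outcome scores patients who enter with mild ARDS as improved at baseline, so for them it measures not falling below a PaO2/FiO2 of 200 rather than improvement

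*Protocol article*

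**What the plan says.** - **Outcome.** Section 4.4 lists as its first secondary outcome "Improvement in oxygen saturation [time frame: 2 weeks"], and defines it as "PaO2/FiO2 ≥ 200 or increase from baseline by 100". The abstract repeats the definition. The two branches are joined by *or*, and only the second refers to the patient's baseline.
- **Eligibility.** Section 4.2 admits "Patients with ARDS as per Berlin definition" aged 18 or over, with no upper or lower limit on PaO2/FiO2.
- **Severity classes.** The Introduction sets out the Berlin definition. It opens the oxygenation criterion with "A moderate to severe impairment of oxygenation must be present", and within the same item lists "Mild ARDS – The PaO_2_/FiO_2_ is >200 mm Hg, but ≤300 mm Hg", followed by the moderate and severe classes.
- **Exclusions.** The eight criteria in section 4.3 concern consciousness, pregnancy, haemodynamics, obesity, tracheostomy, pH, glaucoma and vertigo. None depends on PaO2/FiO2.
- **Objective.** Section 2 puts improvement in oxygenation first among the secondary aims, as something to explore.

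**The concern.** The cut-off of 200 works as a target for a patient who starts below it. Mild ARDS lies above it, and mild ARDS is eligible. A patient who enters at 250 and stays at 250 is counted as improved, and so is one who drops from 290 to 205. A moderate patient who rises from 150 to 199 is not. The label and the scoring rule disagree for an entire severity class.

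If most mild patients score as responders whatever interface they receive, they raise the response rate in both arms and pull the two rates together. The outcome would then understate a real oxygenation benefit of the helmet and report a high improvement rate that partly describes who was enrolled. This is a fault in a definition that the article states in full, so an analysis plan that applied it faithfully would carry it forward.

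**Working it through.** **1. Logic check.** Let *b* be baseline and *f* follow-up PaO2/FiO2 in mm Hg. As written, improved = (*f* ≥ 200) or (*f* − *b* ≥ 100). The article states no figure for this outcome, so there is nothing to reproduce first.

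| Baseline | Follow-up | Change | Scored improved? |
|---|---|---|---|
| 250 | 250 | 0 | yes |
| 290 | 205 | −85 | yes |
| 300 | 200 | −100 | yes |
| 210 | 199 | −11 | no |
| 150 | 199 | +49 | no |

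Every integer baseline from 201 to 300 (100 of 100) satisfies the rule with *f* = *b*. The largest fall still counted as improvement is 100, from 300 to 200. No mild patient assessed below 200 is counted. A moderate patient at exactly 200 also satisfies the rule at entry.

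**2. Dilution, worst case.** Inputs: 60 patients in total (section 4.6), taken as 30 per arm. The following are assumptions, not in the article: response *r* of 60% versus 30% in moderate and severe patients, mild share *m* equal in the two arms, and mild patients scored as responders 100% of the time in both arms.

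Response rate per arm = *m* + (1 − *m*) × *r*. The difference is (1 − *m*) × (0.60 − 0.30). Power is by exact enumeration of two binomials with the pooled two-sided z-test at 0.05.

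| Mild share | Response rates | Difference | Power |
|---|---|---|---|
| 0% | 60% v 30% | 30 points | 66% |
| 20% | 68% v 44% | 24 points | 47% |
| 30% | 72% v 51% | 21 points | 38% |
| 40% | 76% v 58% | 18 points | 31% |

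**3. If mild patients do not all respond.** Suppose instead that mild patients stay at or above 200 in 85% versus 60% (assumed). At a 30% mild share the rates are 0.3 × 0.85 + 0.7 × 0.60 = 67.5% and 0.3 × 0.60 + 0.7 × 0.30 = 39.0%. The difference is 28.5 points and power is 62%. The loss is then small.

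**4. Two possible repairs, at a 30% mild share.**
- Require a rise of 100 from everyone who starts at 200 or more. If no mild patient achieves it, the rates are 0.7 × 0.60 = 42% and 0.7 × 0.30 = 21%, and power is 42%.
- Restrict the outcome to baseline below 200. This leaves 0.7 × 30 = 21 per arm at 60% versus 30%, and power is 49%.

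**The case against.** **Mild patients can still fail.** It is tempting to say that the outcome is met by definition in mild ARDS and tells us nothing about the interface. The documents do not support that. The outcome is assessed over two weeks, not on the entry blood gas, and a mild patient assessed below 200 without a rise of 100 is not scored improved. Staying at or above 200 could differ between helmet and mask. What remains is that this is maintenance, not improvement. The article does not say which reading in the window decides. If any single reading were enough, a mild patient's first qualifying reading would settle the score, but that cannot be assumed.

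**The mild share may be small.** Section 5.1 includes PaO2/FiO2 above 150 at a PEEP of 5 cm H2O among its conditions for discontinuing NIV, and a mild patient at that PEEP meets that part at entry. Few such patients may be enrolled. That limits the size of the problem but does not remove it, because nothing excludes them.

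**Chance imbalance in severity.** A reader might infer that the definition manufactures false effects when one arm has more mild patients. At a 30% share, the arms differ by four or more mild patients with probability 0.32. Those patients would otherwise respond at 30% to 60% under the assumptions above, so four extra shift a rate by 4/30 × 0.4 to 4/30 × 0.7, about 5 to 9 points. The test already allows for such variation: with both arms at 51%, it rejects with probability 0.052. This is not a separate fault.

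**The phrase about moderate to severe impairment.** It does not exclude mild ARDS, because the same item goes on to list the mild class.

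**Conclusion.** The point holds as a definitional flaw in one of seven secondary outcomes. For any patient entering above 200, the scoring rule counts no change, and a fall of up to 100, as improvement. This follows from the article's own text and needs no assumption.

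The size is uncertain. The drop in power from 66% to 38% at a 30% mild share rests on an assumed 60% versus 30% response in the other patients, an assumed mild share, and near-universal response among mild patients in both arms. It should be read as a worst case. If the interface affects whether mild patients stay above 200, the loss can be slight. The article claims no power for this outcome and words the objective as exploratory. The primary outcome does not use PaO2/FiO2 thresholds of this kind and is unaffected.

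**What to change.** In section 4.4 and the abstract, restrict the responder outcome to patients whose baseline PaO2/FiO2 is below 200, and say so. Alongside it, report change in PaO2/FiO2 from baseline for all patients, so that mild patients still contribute to the oxygenation objective. Both use the blood gases that section 5.1 already has monitored in each arm.

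The restriction is preferable to keeping everyone and demanding a rise of 100 from those who start at 200 or more. Under that rule a patient at 290 must reach 390 while one at 199 needs a single point, so near-automatic responders become near-automatic non-responders and little power is recovered (42%, against 38% as written and 49% with the restriction, on the assumptions above).

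The cost is a sentence or two in the definition. Fewer patients enter the responder comparison, and the reported response rate will be lower.

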## Abstract

**Abstract:**

The main aim of this study is to compare the use of non-invasive ventilation (NIV) via helmet versus face mask where different interfaces and masks can apply NIV. However, some of the limitations of the NIV face mask were air leak, face mask intolerance, and requirement of high positive end expiratory pressure, which could be resolved with the use of the helmet NIV. NIV facemask will be applied as per the facial contour of the patient. NIV helmet is a transparent hood and size will be measured as per the head size. Both groups will have a standard protocol for titration of NIV.

Patients aged more than 18 years old and diagnosed with acute respiratory distress syndrome as per Berlin definition will be enrolled in the study after signing the informed consent. Subjects who met the inclusion criteria will receive 1 of the 2 interventions; blood gases, oxygenation status [Po2/Fio2] will be monitored in both groups. The time of intubation will be the main comparison factor among the 2 groups. The primary and secondary outcomes will be measured by the number of patients requiring endotracheal intubation after application of helmet device, Improvement of oxygenation defined as PaO2/FiO2 ≥ 200 or increase from baseline by 100, duration of mechanical ventilation via an endotracheal tube, intensive care unit length of stay, death from any cause during hospitalization at the time of enrolment, need for proning during the hospital stay, intensive care unit mortality, and the degree to which overt adverse effects of a drug can be tolerated by a patient including feeding tolerance.

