## Objectives

2

Primary objective: To assess the efficacy of non-invasive ventilation with HELMET in reducing endotracheal intubation rates in comparison with NIV face mask among patients with ARDS.

Secondary objective: to explore any improvement in oxygenation, time to intubation, ventilation days, and tolerance to HELMET NIV in comparison with facemask NIV.

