### Statistical methods

5.3

Data analysis will be carried out by the principal investigator with the help of a biostatistician. Descriptive statistics will be used to summarize and determine the sample characteristics and distribution of parameters related to demographic, presenting signs and symptoms, laboratory findings. The normally distributed data and results will be reported with mean and standard deviation with corresponding 95% confidence interval.

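### Secondary outcome 2 is labelled ventilator-free days but defined as time on the ventilator; the two run in opposite directions and can rank the arms differently once patients die

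*Protocol article*

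**What the plan says.** All references are to the protocol article.

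- **Outcomes measures (4.4), secondary outcome 2:** "Ventilator-free days [time frame: 28 days]Duration of mechanical ventilation via endotracheal tube". The name and the description stand in one entry.
- **Abstract:** the outcome list has "duration of mechanical ventilation via an endotracheal tube, intensive care unit length of stay, death from any cause during hospitalization". It does not mention ventilator-free days.
- **Objectives (2):** the secondary objective is "to explore any improvement in oxygenation, time to intubation, ventilation days, and tolerance to HELMET NIV". Here the term is again days on the ventilator.
- **Outcomes measures, secondary outcome 6:** death in the same 28-day window is a separate outcome, "ICU mortality [time frame: 28 days]Death from any cause during ICU hospitalization at the time of enrollment". Overall mortality is listed as well. Neither is combined with outcome 2.
- **Statistical methods (5.3):** "The normally distributed data and results will be reported with mean and standard deviation with corresponding 95% confidence interval". This does not settle which quantity outcome 2 is.

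**The concern.** The name and the definition describe different quantities with opposite directions of benefit. That would be a slip of terminology if one could always be converted into the other, but it cannot. A patient who dies stops accumulating ventilator days. Time on the ventilator as defined therefore improves with early death, whereas ventilator-free days, as usually scored, give that patient the worst value. The population has acute respiratory distress syndrome and the protocol lists 28-day ICU mortality as an outcome, so deaths in the window are expected.

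Two things are at stake. An interface with more early deaths could look better on the defined outcome and worse on the labelled one. And because both readings have support in the text, either could be reported as the planned outcome after the results are known.

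**Working it through.** The article gives no expected value, power or effect size for this outcome, so there is no figure to reproduce. The check compares the stated wordings and then scores assumed patients both ways.

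**1. The wordings side by side**

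| Place | Quantity named | Better when |
|---|---|---|
| Outcomes measures, label of outcome 2 | Days free of the ventilator | Higher |
| Outcomes measures, definition of outcome 2 | Time ventilated through a tube | Lower |
| Abstract | Time ventilated through a tube | Lower |
| Objectives | Days on the ventilator | Lower |

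Three of the four say time on the ventilator; the label is the outlier.

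**2. How the two quantities relate**

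Let D be ventilated days up to day 28, with 0 for a patient never intubated. Let V be ventilator-free days under the usual convention: V = 28 − D if alive at day 28, and V = 0 if dead by day 28. Both scoring rules are assumptions; the article states neither.

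If nobody dies by day 28, the difference between arms in mean V is the difference in mean D with the sign reversed, and only the direction of reading is at issue. With deaths, this relation fails.

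**3. Assumed patients scored both ways**

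| Patient | D | V |
|---|---|---|
| Never intubated, alive | 0 | 28 |
| Ventilated 10 days, alive | 10 | 28 − 10 = 18 |
| Intubated day 1, dies day 3 | 2 | 0 |
| Never intubated, dies day 2 | 0 | 0 |
| Intubated day 1, dies day 27 | 26 | 0 |

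On D, the day-3 death (2) beats the survivor ventilated for 10 days (10). On V, the survivor wins, 18 to 0. On D, the never-intubated patient who dies on day 2 ties with the never-intubated survivor.

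**4. Effect on a mean, early deaths**

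Replace a share q of survivors with D = 10 by day-3 deaths with D = 2:

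- mean D = 10(1 − q) + 2q
- mean V = 18(1 − q)

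| q | Mean D | Mean V |
|---|---|---|
| 0% | 10.0 | 18.0 |
| 20% | 8.0 + 0.4 = 8.4 | 14.4 |
| 40% | 6.0 + 0.8 = 6.8 | 10.8 |

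D appears to improve as deaths rise, while V worsens.

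**5. A second set of assumptions, including never-intubated patients**

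Suppose 40% are intubated, intubated survivors are ventilated for 12 days, intubated patients who die are ventilated for 5 days, and every never-intubated patient survives.

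- 30% of intubated patients die: mean D = 0.4 × (0.7 × 12 + 0.3 × 5) = 3.96; mean V = 0.6 × 28 + 0.4 × 0.7 × 16 = 21.28.
- 70% die: mean D = 0.4 × (0.3 × 12 + 0.7 × 5) = 2.84; mean V = 0.6 × 28 + 0.4 × 0.3 × 16 = 18.72.

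The direction is the same, with smaller changes: D falls by 1.12 days and V by 2.56.

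**6. Where the reversal stops**

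It needs deaths to have fewer ventilated days than the survivors they replace. If the deaths in step 4 were instead the day-27 kind (D = 26), then at q = 40% mean D = 6.0 + 10.4 = 16.4 and mean V = 10.8. Both then worsen together. The conflict in ranking comes from early deaths, not from all deaths.

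**The case against.** The strongest reply is that the intended quantity is recoverable. The definition, the Abstract and the Objectives all give time on the ventilator. This stands in part: a reader might infer that the direction favouring the helmet cannot be told at all, and that goes too far. It does not remove the contradiction, because the registered-style name of the outcome still says the reverse, and an analysis plan that is not shown cannot make the two halves of this entry agree.

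Other stronger readings are tempting and the document does not support them:

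- **That the missing rule for deaths is itself an error.** A journal article commonly leaves this to the full protocol or analysis plan, neither of which is shown. The point rests on the stated definitions. The early-death criticism applies to duration as defined, not to ventilator-free days as usually scored.
- **That ICU length of stay has the same defect.** The entry is "Intensive care unit length of stay [time frame: 4 weeks]The number of days admitted to the intensive care unit", where name, definition and time frame agree. It does shorten with death, but that is a general limitation of length of stay. Replacing it would be a preference.
- **That duration will be compared only among intubated patients, and so conditioned on the primary outcome.** Nothing says so. With the intubation rates cited in the Introduction (61.5% and 18.2%) and an assumed 30 per arm, it would leave 30 × 0.615 ≈ 18 against 30 × 0.182 ≈ 5 patients; the article gives only the total of 60.
- **That harm would be hidden.** Mortality is reported separately, so excess deaths would appear beside any apparent shortening of ventilation.
- **That the numbers forecast this trial.** Intubation shares, ventilated days and death rates in the illustrations are assumed, and a rise in deaths from 30% to 70% is extreme.

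**Conclusion.** The concern holds for secondary outcome 2. Its label and its definition have opposite directions of benefit and are complements only in patients alive at day 28. With early deaths the two can order the arms differently. In the illustrations, duration looked better by 1.12 to 3.2 days while ventilator-free days fell by 2.56 to 7.2. Those sizes rest on assumed patients and on the usual convention of scoring death as 0; they show the mechanism and are not estimates for this trial.

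It should be fixed, but it does not threaten the trial's main conclusion. This is one of seven secondary outcomes, the secondary objective is worded as exploratory, and the primary intubation outcome is unaffected.

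**What to change.** Choose one quantity and use it in the Abstract, the Objectives and the Outcomes measures section, so that label and definition match everywhere.

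The preferred choice is ventilator-free days to day 28 from randomisation: days alive and free of invasive ventilation, in all randomised patients, with death by day 28 scored 0 and never-intubated survivors scored 28. Compare the arms with a rank-based method, since values will gather at 0 and 28. Report raw time on the ventilator descriptively. If duration is kept as the outcome instead, drop the ventilator-free label and state how deaths are handled.

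The cost is a rewording in three places and one item of follow-up. The listed mortality outcomes concern death in hospital or in the ICU, so vital status at day 28 would have to be confirmed for patients discharged earlier. Treatment and sample size do not change.

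As advice only: present ICU length of stay beside mortality or by survival status.

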NIV can be applied by different interfaces and masks. The limitations of the face mask NIV that are found in some studies were air leak, face mask intolerance, and requirement of high PEEP.^[15–17]^

These obstacles were overcome to some extent by the introduction of helmet NIV. It provided better patient tolerance, less air leak as there is no contact with the facial tissues, and a better seal at the neck level. To our knowledge, there is only 1 randomized trial that compared the effects of helmet NIV versus face mask NIV in preventing endotracheal intubation.^[18]^ The results of the trial showed the intubation rate was 61.5% (n = 24) for the face mask group and 18.2% (n = 8) for the helmet group (absolute difference, –43.3%; 95% CI, –62.4% to –24.3%; *P* < .001). As evidenced from the mentioned trial, we hypothesize the use of an NIV helmet can reduce intubation in ARDS caused by pneumonia, including COVID-19.

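### Secondary outcome 4 is labelled overall mortality over 90 days but counts only deaths in the enrolment admission, so it cannot be reported as 90-day all-cause mortality

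*Protocol article*

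**What the plan says.** Section 4.4 (Outcomes measures) gives label, window and definition in one entry. The label and window are "Overall mortality [time frame: 90 days", and the definition that follows directly is "Death from any cause during hospitalization at the time of enrollment". The abstract lists the same outcome as "death from any cause during hospitalization at the time of enrolment", with no 90-day window.

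Three other statements bear on how far the point reaches:

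- The companion outcome in section 4.4 reads "ICU mortality [time frame: 28 days]Death from any cause during ICU hospitalization at the time of enrollment".
- The only length-of-stay outcome in section 4.4 concerns the ICU: "Intensive care unit length of stay [time frame: 4 weeks]The number of days admitted to the intensive care unit".
- The Introduction states the expected effect of the helmet in terms of intubation: "we hypothesize the use of an NIV helmet can reduce intubation in ARDS caused by pneumonia, including COVID-19".

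**The concern.** The label and window describe one quantity, vital status at 90 days from any cause. The definition describes another, death before leaving hospital in the admission during which the patient was enrolled. They count different deaths. An analyst who follows the definition reports in-hospital mortality under a heading that readers will take as 90-day survival status. An analyst who follows the heading reports something the definition does not allow.

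There is also a comparability question. When observation for death ends at discharge, the time during which a death can be counted equals the patient's hospital stay. If stays differ between arms, so does that time.

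Mortality in critically ill patients will be read closely even as a secondary outcome, so the plan should fix which deaths count before analysis.

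**Working it through.** There is no stated figure to reproduce. The check is first one of reading, then a short illustration of scale.

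**1. Which deaths are counted**

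Apply the possible readings of the entry to four kinds of patient.

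| Patient | Label and window: all-cause death by day 90 | Definition alone | Definition with 90 days as a cap |
|---|---|---|---|
| Dies in the enrolment admission by day 90 | counted | counted | counted |
| Discharged on day 15, dies at home on day 40 | counted | not counted | not counted |
| Discharged, readmitted, dies before day 90 | counted | not counted | not counted |
| Dies in the enrolment admission after day 90 | not counted | counted | not counted |

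The readings agree only on the first row. Both readings that respect the definition omit every death between discharge and day 90.

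**2. Whether the ICU outcome has the same fault**

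Its label says ICU mortality and its definition counts deaths during the ICU stay. Label and definition agree, so there is no contradiction.

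**3. Scale of a missed death**

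Input: 60 patients in total (section 4.6). Equal arms of 30 are assumed; the article does not state arm sizes.

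One missed death: 1/30 = 3.3 percentage points in that arm.

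**4. What unequal stays could do (all rates assumed)**

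Let m be true 90-day mortality, the same in both arms, and f the share of those deaths that occur after discharge. Then

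observed in-hospital mortality = m × (1 − f), and expected missed deaths per arm = 30 × m × f.

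Call the arms A and B.

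| m | f in A | f in B | Observed A | Observed B | Spurious difference | Missed deaths A, B |
|---|---|---|---|---|---|---|
| 20% | 5% | 25% | 19% | 15% | 4 points | 0.3, 1.5 |
| 30% | 5% | 25% | 28.5% | 22.5% | 6 points | 0.45, 2.25 |
| 40% | 5% | 25% | 38% | 30% | 8 points | 0.6, 3.0 |
| 20% | 5% | 15% | 19% | 17% | 2 points | 0.3, 0.9 |
| 40% | 5% | 15% | 38% | 34% | 4 points | 0.6, 1.8 |
| 20% | 10% | 10% | 18% | 18% | 0 | 0.6, 0.6 |
| 40% | 10% | 10% | 36% | 36% | 0 | 1.2, 1.2 |

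Two things follow. Deaths are missed in every row, so the label is wrong whatever the stays are. A spurious difference appears only when f differs between arms, and its sign reverses if A and B change places. The documents give no value for m, for f or for hospital stay, so the table shows what is possible and not what is expected.

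**The case against.** The best defence is that the entry is loosely worded but coherent. The proning outcome in the same list has the same build: a time frame of up to 24 weeks for an event limited to the hospital stay. Read alike, the mortality entry means in-hospital death, observed for at most 90 days, with overall meaning not only in the ICU. The abstract supports this, because it gives the in-hospital definition alone. The definition is also disclosed, so a careful reader is not deceived. This reading is possible and it would settle the deaths after day 90. It does not rescue the label: what is counted would still not be overall mortality at 90 days, and the proning entry at least says up to.

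A second defence is that a journal article condenses a fuller protocol. That disposes of any complaint that no day-90 follow-up procedure is described, and none is made here. It does not dispose of a conflict between heading and definition that the article itself prints.

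The remaining objections are to stronger readings, and they succeed:

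- A reader might infer that the helmet shortens stay and that mortality is therefore biased in its favour. The Introduction predicts fewer intubations only. No section predicts a shorter hospital stay, and the length-of-stay outcome concerns the ICU, whereas this mortality outcome is bounded by hospital discharge. A shorter stay would not suffice either: bias at equal mortality needs a different share of deaths after discharge, and patients may leave earlier because they have recovered.
- A reader might try to size the bias by supposing a mean stay for each arm. A mean is not a common discharge day, and deaths after discharge are lost in both arms over a 90-day window.
- A reader might extend the point to ICU mortality. Leaving out ward deaths is what that term means, so replacing the outcome would be a preference and not a correction.

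**Conclusion.** The point holds for secondary outcome 4. Its heading promises 90-day overall mortality, its definition delivers in-hospital mortality, and deaths between discharge and day 90 are not counted. This follows from the printed text and needs no assumption.

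The possibility of bias is conditional. It arises if hospital stay, and with it the share of deaths after discharge, differs between arms. Its direction and size cannot be computed from the document. The 3.3 points per missed death rests on equal arms of 30, and the 2 to 8 point differences rest on assumed rates; with equal shares after discharge and equal mortality the difference is nil.

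The reach is limited. This is one of seven secondary outcomes, and the ICU mortality outcome is consistent as it stands. The primary outcome, need for intubation, is unaffected. The definition should be corrected before analysis, because it decides which deaths are counted and what may be claimed from them.

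**What to change.** Preferred: define outcome 4 as death from any cause within 90 days of randomisation, in or out of hospital. Obtain vital status at day 90 from records or a telephone call. Anchoring the window at randomisation matches the tolerability outcome in the same list. Keep death during the enrolment admission as a separately named outcome, and align the abstract.

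The cost is a change of wording and one vital-status check for at most 60 patients. The small downside is that follow-up effort, and any patient whose day-90 status cannot be found should be reported as such and not scored alive.

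If follow-up after discharge is not wanted, rename the outcome in-hospital mortality and state 90 days only as a cap on the period in hospital. This costs wording alone. It removes the contradiction, but observation still ends at discharge, so the result should be reported as in-hospital mortality with that limitation stated. ICU mortality need not be changed under either option.
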